## **3.6 Statistical analysis**

The sample's demographic characteristics, descriptive data, age, education, race, and ethnicity will be described using the mean and standard deviation or frequencies and proportions as appropriate.

In the 1st study, based on the results of the pre-test and post-test in only TC exercise group, both Paired t-test and McNemar test will be used to explore differences in the outcomes that are response time and error ratio in SCWT, and LF, HF, LF/HF, Mean BPM, SDNN and RMSSD in HRV test.

In the 2nd study, there will also be three levels of outcomes in both TC exercise  
Version number 2.0 ; Dated 15thFeb. 2022

group and control group. The primary outcomes are response time and error ratio in SCWT; LF, HF, LF/HF, Mean BPM, SDNN and RMSSD in HRV test; Average power in EEG. The secondary outcomes are body fat, BMI, body fat ratio in body composition; and vital capacity, balance, handgrip strength, vertical jump, and sit and reach flexibility in PF. And the tertiary outcomes are depression and anxiety on psychological scales. Two-way repeated measures ANOVA will be performed with 2 levels in the group factor (Group: TC, Control) and 2 levels in the time factor (Time: pre-test1, post-test2) to assess three levels of outcomes. All analyses will be conducted with IBM SPSS 26.0, with the statistical significance level set at  $p \leq 0.05$ .

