## **1.2 Scope of the study**

The scope of this study includes the 1st and 2nd study.

The 1st study is to determine the effects after single practice of TC. As we all know that TC is a safe neurobiological complementary therapy, however, throughout the course of life, both function and organization of the human brain are plastic (Kurth et al., 2015), and some of the neurobiological effects appear to be partially

Version number2.0 ; Dated 15thFeb. 2022

reversible (NIDA, 2021). Hence, it is necessary to determine the effects after the single practice of TC exercise with a within-subject design in participants already receiving TC exercise groups.

The 2nd study is to evaluate whether the long-term effects of 12 weeks of TC training can be used as exercise intervention to improve cognitive performance, mental health, and PF by comparing within two-arm, randomized, parallel controlled groups. In addition, a follow-up evaluation will be conducted in the fourth week.

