### **1.5 Study hypothesis**

Hypothesis 1: It exists additive effect of TC, and single practice of TC intervention can affect the outcome parameters of the related physiological experiment, and deserve well of SCWT and HRV performance.

Hypothesis 2: TC can be used as an exercise intervention to improve cognitive performance, mental health, and PF in the 2nd study, and the 2nd study will be conducted by comparing the parameters related to the outcome before and after performing 12 weeks of TC between the two groups.

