### **3.3.2 Test sequence**

Following informed consent.

In the 1st study, all participants in TC exercise group will be assessed before and after a 45-minutes TC training session in 4th week to determine the effects of single TC training session. Both pre-test2 and post-test1 will be in the following order: 1)SCWT, and 2) HRV test.

In the 2nd study, all participants in both TC exercise group and control group will be assessed before and after 12-weeks to evaluate the long-term effects of TC training session. Both pre-test1 and post-test2 will be in the following order: 1)DSI and STAI, 2) SCWT, 3)HRV test, 4)PF test and Body Scale, and 5)rs-EEG.

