### **3.4.3 Stroop color word test**

The SCWT consisted of two sessions: word recognition (WR); color recognition (CR), and used software Eprime 2.0 Professional (Psychology SoftwareTools, Inc., Pittsburgh, PA), which allows online recording and voice-key triggering of the participants' verbal responses, for presenting the stimuli and collecting the data.

In order to further reduce the non-specific interfering factors of the Stroop task, such as practice times, stimulus encoding, contextual factors, color name facility, operational tasks, the amount of SOA, the subject's age and mood, the proportion of words and non-words (Rezaei, M., 2019; Edwards, S. et al., 1996), The stimuli were four-color word names presented in Chinese word as 红(RED), 黄(YELLOW), 蓝(BLUE) and 绿(GREEN). SCWT will produce two types of situations. In the case of the same word color, the meaning of the word matches the color ink. For example, the word BLUE is presented in blue ink; when the word color is inconsistent, the meaning of the word conflicts with the color of the ink. , Such as the word BLUE in red ink (Zhu, 2020). Participants will be asked to choose any a key (f, j, r, u) based on the word presented in four colors: red, yellow, blue, or green. The four colors used the left index finger, the right index finger, the left middle finger, and the right middle finger, respectively. For example, if the word color is yellow, whatever the word, the correct response is to press the "j" key with the right index finger. The stimulus consisted of randomly matched colors and words (120 incongruent trials, 40 congruent trials). All stimuli were presented for 500 ms followed by fixation point (+) for 250ms and a

stimulus remained displayed on the screen for a maximal duration of 1000 ms, see figure 4. The conflict effect of the two groups before and after inhibitory control training was evaluated through response time and error rate in both the congruent and incongruent stimulus (Xu et al., 2021). All subjects are required to practice until the correct rate is higher than 60% before the formal test can be conducted.

[figure not shown]

**Figure 4** SCWT process

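### Study 1 assigns McNemar's test to outcomes none of which is binary, and reads a TC-only before–after change as the effect of one session

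*Protocol*

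**What the plan says.** Section 3.6 gives one sentence of analysis for Study 1. It uses pre-test2 and post-test1 "in only TC exercise group" and says that "both Paired t-test and McNemar test will be used to explore differences in the outcomes that are response time and error ratio in SCWT", continuing the same list with "LF, HF, LF/HF, Mean BPM, SDNN and RMSSD in HRV test". Neither test is tied to particular outcomes; both cover all eight.

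Section 3.4.3 describes the Stroop task as "120 incongruent trials, 40 congruent trials", with performance "evaluated through response time and error rate in both the congruent and incongruent stimulus". It also names practice among the task's interfering factors, and requires more than 60% correct in practice before the formal test.

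Section 3.3.2 places the two Study 1 tests before and after one 45-minute TC session in week 4, "to determine the effects of single TC training session". Section 3.1 identifies it as the 12th session. Controls are tested only at pre-test1 and post-test2.

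Section 1.2 describes the aim as being to "determine the effects after the single practice of TC exercise with a within-subject design in participants already receiving TC exercise groups". Hypothesis 1 in section 1.5 is causal: "single practice of TC intervention can affect the outcome parameters of the related physiological experiment". Section 1.4 ranks this aim as tertiary.

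**The concern.** There are two separate faults in the same short plan.

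**The test does not match the data.** McNemar's test compares discordant yes/no pairs. With no binary endpoint among the listed outcomes, the analyst would have to invent one or change the unit of analysis after seeing the data. Either step decides the result and neither is fixed in advance.

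**The inference does not match the design.** A before–after change in one arm is the sum of any session effect, retest practice, time, and the ordinary response of heart rate and HRV to any exercise. Choosing the right paired test does not separate these parts. If a significant change is reported as the effect of one TC session, Hypothesis 1 could be declared supported when TC contributed nothing.

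**Working it through.** **1. The protocol's own sample size.** The only stated size is for Study 2: 20 per group for 80% power, raised to 25 per group (section 3.2.2). From means 0.392 and 0.475 and SDs 0.087 and 0.097: (1.96 + 0.84)² × (0.087² + 0.097²) / 0.083² = 19.3, so 20 per group. The figure reproduces. It does not size Study 1, but it caps it at 25 participants.

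**2. Outcome type against McNemar's requirement.**

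| Study 1 outcome | Type per participant | Binary? |
|---|---|---|
| Stroop response time | continuous | no |
| Stroop error ratio | proportion, k/160 (120 + 40 trials) | no |
| LF, HF, LF/HF | continuous | no |
| Mean BPM, SDNN, RMSSD | continuous | no |

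None of the eight qualifies. The 60% rule is an entry condition before the test, not an outcome.

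**3. What would happen if McNemar were forced.** Two routes exist. The inputs here are assumptions, not protocol figures: 25 participants, 160 trials, about 10% errors, between-person SD 0.5 logit, no average change.

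- *Dichotomise each participant's error ratio.* The exact test gives type I error of about 1% to 2%. It is conservative and discards information: with 5 discordant pairs all in one direction the two-sided p is 2 × 0.5⁵ = 0.0625, so at least 6 are needed (2 × 0.5⁶ = 0.031).
- *Pool individual trials.* Here the statistic is (B − C)²/(B + C), with B and C the discordant trial counts over all participants. Simulated type I error is about 5% with no person-by-session variation, and about 13%, 22% and 40% when an independent shift with SD 0.2, 0.3 or 0.5 logit is added to each person's log-odds at each session. The paired t-test on participants' error ratios stays at about 5% throughout.

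**4. The uncontrolled contrast.** Suppose TC has no effect and retesting alone shifts scores by dz standard deviations of the paired difference (assumed range). The rejection probability of the two-sided paired t-test at 0.05 comes from the noncentral t with n − 1 degrees of freedom and noncentrality dz × √n:

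| Assumed dz | n = 20 | n = 25 |
|---|---|---|
| 0.2 | 14% | 16% |
| 0.3 | 25% | 30% |
| 0.5 | 57% | 67% |
| 0.8 | 92% | 97% |

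For example, dz = 0.5 and n = 25 give noncentrality 0.5 × 5 = 2.5 and a rejection probability of 67%.

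**The case against.** The strongest defence is context. The aim is tertiary, section 3.6 says the tests will explore differences, and the within-subject, TC-only design is openly declared. Participants practise to a criterion and have already met the Stroop task at pre-test1, so pre-test2 is not a first exposure. These points limit the importance of the fault and may shrink the retest effect. They do not remove it, they do not address HRV after exercise, and they do not undo the effect wording in sections 1.2, 1.4, 1.5 and 3.3.2.

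On the test itself, the authors may have meant McNemar for errors only. The sentence does not say so, and the error ratio is still not binary. A separate analysis plan could define a binary endpoint, but it would then not be one of the eight outcomes listed.

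Some stronger readings are tempting and are not supported:

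- *That the plan carries a 13% to 40% false-positive rate.* The protocol nowhere proposes pooling trials, and randomly matched colours and words give no natural pairing of one trial before with one after. The dichotomised route is conservative. The range illustrates one possible misuse.
- *That eight tests at 0.05 give a 34% chance of a false positive.* That is 1 − 0.95⁸, which assumes independence, whereas LF/HF is computed from LF and HF. The point made here does not depend on it.
- *That testing controls over the same interval would isolate the session effect.* The TC arm has had about 11 sessions before the 12th, so pre-test2 may already reflect training. A comparison between arms adjusted for pre-test2 would control for retesting, but could mix accumulated training with the single session.

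**Conclusion.** Both faults stand. McNemar's test is wrong as written: it fits none of the eight listed outcomes, and this follows from the protocol's text without any assumption. The before–after change in the TC arm cannot be attributed to one TC session, because nothing at pre-test2 and post-test1 separates it from retest practice or a general exercise response. The size of the second problem depends on a retest shift that the protocol does not give: over an assumed dz of 0.2 to 0.8 with 25 participants, a significant result would arise 16% to 97% of the time with no TC effect. This does not show that a TC effect is absent, only that the design cannot establish it. Severity is moderate, since the aim is tertiary and exploratory and Study 2 is unaffected.

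**What to change.** In section 3.6, delete McNemar's test. Analyse each participant's response time, error ratio and HRV measures with the paired t-test, or the Wilcoxon signed-rank test if the differences are skewed.

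In sections 1.2, 1.4, 1.5, 1.6 and 3.3.2, describe Study 1 as within-group change around one TC session, and state that no causal conclusion about TC will be drawn from it. The first research question in section 1.3 uses the same effect wording and should be aligned.

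A control-arm test over the same interval is not required. It would add testing visits, and would need the caveat about training already accumulated by week 4.

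The cost is one changed sentence in 3.6, consistent rewording in the sections named, and a narrower Study 1 claim. No data collection changes.

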### **1.4 Objective of this study**

This study aims to evaluate the effectiveness of TC on cognitive performance, mental health and PF of sedentary college students.

The primary aims of this study are to evaluate the effect of a 12-week 24-Form TC training in college students with a sedentary lifestyle due to COVID-19 and to explore the underlying mechanism based on SCWT, HRV and resting-state electroencephalogram (rs-EEG).

The secondary aims of this study are as follows:

To investigate the effect of TC on specific domains of body composition and Physical Fitness in college students with a sedentary lifestyle due to COVID-19; And to explore the mechanism of action of TC on mental health, especially in depression and anxiety, in college students with a sedentary lifestyle due to COVID-19 based on HRV.

Meanwhile, the tertiary aims of this study are as follows: To investigate the effect of single practice TC on cognitive performance in college students with a sedentary

Version number 2.0 ; Dated 15thFeb. 2022

lifestyle based on SCWT and HRV test.

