### 3.2.2 Sample size, screening, and allocation

#### (1) Sample size estimation

Depending on the type of data or study design, there are multiple methods that can be used to calculate the sample size. If suppose that the sample sizes of the Version number2.0 ; Dated 15thFeb. 2022

two groups in this design are equal, and compare the means of the two groups, use the following formula to calculate the sample size equation:

$$n = (Z_{crit} + Z_{pow})^2 * 2 * \sigma^2 / d^2 \quad \text{or}$$

$$n = (Z_{crit} + Z_{pow})^2 * (SD_1 + SD_2)^2 / (M_1 - M_2)^2$$

Here, n represents the sample size of each group; assuming that the two groups of samples are the same,  $\sigma^2$  represents the variance of either group; D represents the smallest detectable value between the two sample means. Zcrit and Zpow respectively represent the significance level and the standard normal deviation of 1- $\beta$  power. The standard normal deviation is the realization of the standard normal random variable, For the two-sided test, the Zcrit value is 1.96 and the significance level is 5%. The Zpow is 0.84 at 80% power and 1.28 at 90% power (Wang & Ji, 2020).

To determine the sample size (Lu et al., 2016), data from our previous prospective study on college students show that TC training achieved significant improvement in cognitive performance (TC group:  $0.392 \pm 0.087$ ; Inactive Control group:  $0.475 \pm 0.097$ ) after the seven-week intervention when compared with subjects in the control group (Converse, 2020). Our estimation of sample size was based on the independent Compare 2 Means analysis between the two groups. Calculations were performed with WinPepi software (Abramson, 2011), one of a set of computer programs for epidemiologists. An overall sample size of 40 participants (20 participants per group) achieves an 80% power at the 0.05 significance level. Taking into account the drop-out rate for each group, we expect that a total sample size is 50 participants (25 participants per group).

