#### **3.4.7 rs-EEG measurement**

rs-EEG will be recorded by using the ActiCHamp amplifier with 64-channel active AgCl electrodes (actiCHamp Plus, Brain Products GmbH, Gilching, Germany), and it will be positioned on the scalp according to the modified 10–20 system.

Previous literature showed that Tai Chi can definitely increase alpha power  
Version number 2.0 ; Dated 15th Feb. 2022

during or after TC exercise (Li, X. et al., 2020; Nakatani, Y. et al., 2006), and maybe along with higher beta power and theta power (Liu, Y. et al., 2003; Wayne, P. M. et al., 2014). In order to measure these more accurately, Electrode gel will be inserted into the midfrontal (F3 & F4), central (C3 & C4), anterior temporal (T3 & T4), and parietal (P3 & P4) sites and referenced to the vertex (Cz) during recording (Field, T. et al., 2010). The horizontal electroophthalmogram will record a bipolar configuration between electrodes located on the lateral sides of each eye canthus; and vertical eye movements will be monitored by a bipolar montage located between electrodes above and below the right eye. Recording will be performed using an on-line 50Hz notch filter. After recording, the data will be restored to a rate of 500Hz and the total mean will be re-referenced (Barnett, K. J., 2008). It will apply both off-line filters with a high cut-off frequency of 0.1Hz and a low cut-off frequency of 35Hz. EEG preprocessing will be performed using BrainVisionAnalyzer software (BrainVisionAnalyzer, Brain Products GmbH, Gilching, Germany).

The whole process lasts eight minutes, EEG will be selected and recorded for three minutes (Gasser et al., 1996), see figure 6. Power spectrum will be computed during the HRV test. Spectral power analysis will be performed at four-second intervals by first applying the Welch window to the data and executing FFT. If the signal from three or more sites for that particular period exceeds  $100\mu\text{V}$ , the period will be rejected. The power spectrum will be averaged for each electrode and calculated for each band: alpha (8 -- 13Hz), beta (14.5 -- 30Hz), delta (0.5 -- 3.5Hz), and theta (4 -- 7.5Hz).

[figure not shown]

**Figure 6** rs-EEG measurement process

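### Nine primary outcomes are each tested at p ≤ 0.05 with no lead outcome, order or adjustment, while the sample size covers one cognitive comparison at 0.05

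*Protocol*

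**What the plan says.** Section 3.6 sorts the outcomes of the 12-week randomised comparison into primary, secondary and tertiary levels. On the primary level it says: "The primary outcomes are response time and error ratio in SCWT; LF, HF, LF/HF, Mean BPM, SDNN and RMSSD in HRV test". It then adds "Average power in EEG". That makes two SCWT outcomes, six HRV outcomes and one EEG outcome.

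One test serves every level: "Two-way repeated measures ANOVA will be performed with 2 levels in the group factor", crossed with two time points, pre-test1 and post-test2. One significance level serves every test: "All analyses will be conducted with IBM SPSS 26.0, with the statistical significance level set at" p ≤ 0.05.

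Section 3.2.2 describes the sample size as follows: "Our estimation of sample size was based on the independent Compare 2 Means analysis between the two groups". It uses one cognitive measure, with means and SDs of 0.392 ± 0.087 (TC) and 0.475 ± 0.097 (control). It arrives at 20 per group for 80% power at 0.05, raised to 25 per group for drop-out.

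Two measurement sections bear on the count. On EEG, section 3.4.7 says: "The power spectrum will be averaged for each electrode and calculated for each band", and it lists four bands and eight named sites. Section 3.4.3 evaluates the SCWT conflict effect through response time and error rate on congruent and incongruent trials. Section 3.6 chooses no band, site or trial type.

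**The concern.** Within the primary level the protocol gives no lead outcome, testing order, division of alpha, adjustment or all-must-succeed rule. The three levels are labels with no gatekeeping between them. As written, a significant SDNN or mean heart rate with nothing on SCWT could be presented as a positive primary result. A mixed result, which is plausible with nine outcomes, has no defined reading.

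The design and the analysis also do not match. The 80% power belongs to one comparison at 0.05. Nine primary outcomes cannot be kept with overall error held at 5% and that power retained at the planned size.

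**Working it through.** **1. The protocol's own figure.**

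- Difference in means: 0.475 − 0.392 = 0.083.
- Pooled SD: √[(0.087² + 0.097²)/2] = 0.0921.
- Standardised effect: 0.083/0.0921 = 0.90.
- n per group: (1.96 + 0.84)² × (0.087² + 0.097²)/0.083² = 19.3, so 20.
- The drop-out rate is not stated, but 20/(1 − 0.20) = 25, so the step to 25 implies 20%.

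Both sizes reproduce. Power at 20 per group is 81% by the normal approximation and 79% by the exact t-test. This holds for one outcome at two-sided 0.05.

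**2. Number of primary tests.** 2 (SCWT) + 6 (HRV) + 1 (EEG) = 9.

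**3. Chance of at least one false positive when TC has no effect,** each test at 0.05 and any one success counting. For independent outcomes this is 1 − 0.95⁹ = 0.370. For correlated outcomes it was simulated with two-sided z tests (1,000,000 draws). The correlations are assumptions.

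| Common correlation (assumed) | Nine tests |
|---|---|
| 0 | 37% |
| 0.3 | 33% |
| 0.5 | 27% |
| 0.7 | 20% |
| 0.9 | 12% |

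If outcomes correlate only within the SCWT pair and within the HRV six, the figures are 32%, 27% and 21% at within-block correlations of 0.5, 0.7 and 0.9.

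**4. SCWT alone.** Two independent outcomes give 1 − 0.95² = 0.0975, about 10%. Positive correlation lowers this.

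**5. If the unspecified measures multiply.** Four EEG bands instead of one item make 2 + 6 + 4 = 12 tests: 1 − 0.95¹² = 46% if independent, 32% at common correlation 0.5. Splitting both SCWT outcomes by trial type as well makes 4 + 6 + 4 = 14 tests: 1 − 0.95¹⁴ = 51% if independent.

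**6. Power if all nine stay primary.** Bonferroni sets alpha at 0.05/9 = 0.0056. With the planned effect of 0.90:

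| Per group | Exact t-test | Normal approximation |
|---|---|---|
| 20 | 47% | 53% |
| 25 | 61% | 66% |

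By the normal approximation, 80% power would need 33 per group. Holm rejects whenever Bonferroni does, so these powers are lower bounds for Holm. They assume that the planning effect applies to the outcome tested.

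**The case against.** The strongest reply is that only the protocol is at hand and multiplicity is often settled in the SAP. Section 3.6 never says that one success suffices; if all nine had to succeed there would be no inflation. The second part stands, and the figures are conditional on it. The first does not remove the point: the protocol itself chose nine primary outcomes and fixed one level for all analyses. An adjustment elsewhere would depart from that text and would undercut the power stated in 3.2.2.

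Three stronger readings are tempting, and the protocol supports none of them.

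- A reader might take 27% as a floor. It rests on an assumed correlation of 0.5. The six HRV measures come from one 2.5-minute recording, and LF/HF is a ratio of two of the others, so higher correlations are possible and the rate would then be lower.
- A reader might multiply four bands by eight sites and count 32 EEG tests. Section 3.6 lists average EEG power as one item, and 3.4.7 describes signal processing. The choice of band and site is left open; 32 primary tests are not stated.
- A reader might take 27–37% as the chance of a false cognitive claim, since section 1.6 looks to the results as evidence of cognitive benefit. For the 12-week study, section 3.1 assesses cognitive performance by SCWT, and the rate for the two SCWT outcomes as listed is at most about 10%.

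**Conclusion.** The point holds as a defect in what section 3.6 states. If any one significant primary outcome can carry a claim, the overall false-positive rate is 37% under independence and still about 12% at a common correlation of 0.9, more than twice the nominal 5%. Where it falls between these cannot be determined from the protocol. Nine is the count as listed, and the open choices of EEG band, EEG site and SCWT trial type could raise it. The planned size supports one primary outcome at 0.05, not nine with error control. This should be settled before any outcome data are seen.

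**What to change.** In 3.6, name one SCWT measure as the single primary outcome of the 12-week study. The sponsor should choose, before data are seen, between the conflict effect described in 3.4.3 and response time on incongruent trials; the protocol does not rank one above the other. Test it by the group-by-time contrast using pre-test1 and post-test2, two-sided at 0.05. In 3.2.2, state that the planning values refer to that measure or justify their use, because they now carry neither a measure name nor units.

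Make the other SCWT measure, HRV and EEG secondary with Holm adjustment, or label them exploratory. Take alpha power as the lead EEG band, since 3.4.7 expects it to rise.

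If the sponsor prefers to keep all nine as primary, apply Holm across them and restate the power in 3.2.2.

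The cost is wording in 3.6 and 3.2.2, with 1.4 aligned; no new data are needed. The downside is that HRV and EEG lose primary status or, if all nine stay, that the stated power falls.

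A separate tidy-up, which does not affect the primary error rate: section 1.4 lists depression and anxiety under the secondary aims ("And to explore the mechanism of action of TC on mental health"), while 3.6 makes them tertiary outcomes. Put them in the same tier in both places.

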## 3.2 Recruitment and sample

### 3.2.1 Recruitment

Study recruitment will be conducted on the campus of Huzhou University. Preliminary recruitment information and requirements will be posted on both the job flyer and university social pages, and interested potential participants can contact the principal investigator by calling the phone number provided or via email in the job flyer. In the first week before the formal experiment, the principal investigator will arrange a meeting for about an hour was arranged in the Sports Anatomy and Physiology Laboratory at 12 o'clock every day to clarify and explain the specific experimental process, and select eligible volunteers, which include taking PARQ and IPAQ questionnaires, and Control the inclusion and exclusion criteria, select eligible subjects and sign the informed consent form.

In addition, this study will use Stratified Blocked Randomization. An independent statistician will first stratify eligible subjects according to "gender" and "BMI ranges that are underweight (under 18.5 kg/m^2), normal weight (18.5 to 25kg/m^2), overweight (25 to 30kg/m^2), and obese (over 30kg/m^2)", block followed by randomization to TC or control group, ensuring that each subject will be randomly assigned to either intervention or control and there is a balance between the number and the BMI value of subjects in both groups. Finally, eligible volunteers will be randomly assigned to the TC group and the control group by envelope sampling. Of course, during any of the above processes or times, the volunteer can ask questions about the research project, and the researcher will further explain and answer the questions until the volunteer understands. Volunteers can still withdraw from the study at any time without affecting their rights during volunteers participating in this study.

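### Study 2 uses a group-by-time ANOVA with no named treatment term; baseline-adjusted ANCOVA answers the same question more efficiently at the same sample size

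*Protocol*

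**What the plan says.** Protocol Section 3.6 applies one method to all primary, secondary and tertiary outcomes of the 2nd study: "Two-way repeated measures ANOVA will be performed with 2 levels in the group factor (Group: TC, Control) and 2 levels in the time factor". The two times are pre-test1 and post-test2, and the software is SPSS 26.0. No term is singled out as the treatment test, and no baseline covariate or stratification factor is named.

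Three other sections bear on this:

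- Section 1.5 (Hypothesis 2) describes the 2nd study as "comparing the parameters related to the outcome before and after performing 12 weeks of TC between the two groups".
- Section 3.2.1 describes stratified blocked randomisation: "An independent statistician will first stratify eligible subjects according to" gender and four BMI classes, which makes 2 x 4 = 8 strata.
- Section 3.2.2 (1) states: "Our estimation of sample size was based on the independent Compare 2 Means analysis between the two groups". It concludes: "An overall sample size of 40 participants (20 participants per group) achieves an 80% power at the 0.05 significance level". That calculation uses neither a baseline value nor a pre-post correlation.

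**The concern.** A 2 x 2 repeated-measures ANOVA gives three tests: group, time, and group x time. Only group x time compares the change between arms. With two time points it is identical to an unpaired t-test on post minus pre, so it subtracts the full baseline value whatever the pre-post correlation is. When that correlation is modest, subtraction adds noise. ANCOVA instead weights the baseline by how well it predicts the post-test.

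The trial plans to analyse about 40 people, so this choice can decide whether the stated 80% power is reached. The sample size was worked out for two independent means without baseline. The planned test matches that calculation only at one particular correlation.

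**Working it through.** **Inputs.** Section 3.2.2 (1) gives 0.392 (SD 0.087) for TC and 0.475 (SD 0.097) for inactive control, two-sided alpha 0.05 and 20 per group. The correlation r is not in the protocol; 0.3, 0.5, 0.7 and 0.8 are assumed. The SD is taken to be the same at both visits.

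**The protocol's own figure.** The difference is 0.475 - 0.392 = 0.083. The common SD is sqrt[(0.087² + 0.097²)/2] = 0.0921, so the standardised effect is 0.083/0.0921 = 0.901. With the section's first formula, n = (1.96 + 0.84)² x 2 x 0.0921²/0.083² = 19.3, which rounds up to 20 per group. Power at 20 per group is 81.3% by the normal approximation and 79.3% by the noncentral t. The stated sample size reproduces.

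**Variance of the estimated effect**, relative to a comparison of post-test means alone:

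- group x time (change score): 2(1 - r)
- baseline ANCOVA: 1 - r²
- ratio, ANCOVA to change score: (1 - r²)/[2(1 - r)] = (1 + r)/2, which is below 1 for every r below 1.

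**Power at 20 per group** (noncentral t). The effective effect is 0.901/sqrt(variance factor).

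| r (assumed) | Factor, change | Factor, ANCOVA | Ratio | Power, group x time | Power, ANCOVA |
|---|---|---|---|---|---|
| 0.3 | 1.40 | 0.91 | 0.65 | 65.0% | 82.8% |
| 0.5 | 1.00 | 0.75 | 0.75 | 79.3% | 89.3% |
| 0.7 | 0.60 | 0.51 | 0.85 | 94.8% | 97.3% |
| 0.8 | 0.40 | 0.36 | 0.90 | 99.2% | 99.6% |

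The inverse ratios, 1/0.65 = 1.54, 1/0.75 = 1.33 and 1/0.85 = 1.18, mean that the change-score test needs about 54%, 33% and 18% more participants for the same precision at r = 0.3, 0.5 and 0.7.

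**Link to the sample size.** At r = 0.5 the change-score factor is exactly 1, so group x time has the power that was calculated. Below 0.5 it has less. ANCOVA has a factor of at most 1, so it does not fall materially below the planned power at any r.

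**Adding sex and BMI class to the ANCOVA.** This was simulated with 40 analysed, 4000 runs per setting, blocks of 4 and an assumed BMI mix of 15/65/15/5%:

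- Strata unrelated to outcome: power goes from 81.1% to 79.6% at r = 0.3, and from 88.3% to 86.7% at r = 0.5.
- Strata explaining 20% of the variance: power goes from 82.8% to 85.2% at r = 0.3, and from 97.1% to 96.7% at r = 0.7.

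The stratum terms therefore move power by about -2 to +2 points. Nearly all of the gain comes from the baseline covariate. Type I error stayed near 5%.

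**The case against.** The strongest reply is that nothing here is invalid. Under 1:1 randomisation the group x time test is unbiased and holds its error rate. At r = 0.5 it delivers roughly the stated power, and at r = 0.7 about 95%. Many of the fitness outcomes may well have a high pre-post correlation, partly because a large stable sex difference itself raises the overall correlation, and then the ANCOVA gain is small. All of this stands. The point concerns efficiency and clarity, and its size depends on a correlation that the protocol does not give.

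Four stronger readings are tempting, and the documents do not support them.

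- **Omitting the strata makes standard errors too wide.** This does not hold for group x time. A sex or BMI effect that is stable over time cancels in the change score. In a simulation with a sex gap of two within-sex SDs and within-sex r = 0.5, the standard error was 0.313 with or without sex in the model.
- **The trial will read the group main effect.** That term averages in the pre-treatment difference, so it would halve the effect, with simulated power of only 31% to 40% at 40 analysed. But Hypothesis 2 points to the before-after comparison between groups, so this is a possible misreading and not the stated plan.
- **The plan expects 20% drop-out and discards incomplete participants.** Going from 20 to 25 per group implies 20%, but no rate is stated. Section 3.6 says nothing on missing data, which may be handled in an analysis plan that is not shown. ANCOVA on the post-test also loses anyone without a post-test.
- **ANCOVA with strata has no downside.** It uses a few degrees of freedom, sparse BMI classes are likely, and baseline BMI duplicates the pre-test value when BMI is the outcome.

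**Conclusion.** The point holds as an avoidable loss of efficiency and an unnamed treatment contrast, not as an error in the validity of the test. At the protocol's own effect size and 20 per group, baseline ANCOVA gains about 18 points of power at r = 0.3, 10 at r = 0.5 and 2 to 3 at r = 0.7, and next to nothing above about 0.8. The direction is certain for every r below 1. The size rests on the assumed r, on equal SDs at the two visits, and on the 0.90 SD effect carrying over to each outcome. Including sex and BMI aligns the model with the randomisation, but it is not where the gain lies.

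**What to change.** In Section 3.6, replace the 2 x 2 ANOVA as the between-group analysis. For each Study 2 outcome, regress the post-test2 value on group and the pre-test1 value, and add the randomisation factors sex and BMI. Enter BMI as a continuous variable or in merged classes, and omit the BMI term where BMI is the outcome. Report the adjusted difference with its 95% CI.

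If the repeated-measures ANOVA is kept, state that group x time is the treatment test and that the two main effects are not.

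Optionally, fit a mixed model with a common baseline mean, which keeps participants who attended only one of the two visits.

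The cost is wording. No extra participants, measurements or software are needed. With 40 analysed, sex and continuous BMI leave 40 - 5 = 35 error degrees of freedom, against 38 for the change-score test.
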